##### **Secondary endpoints:**

##### **Efficacy endpoints**

- Proportion of subjects who achieved (yes/no) body weight reduction  $\geq 5\%$ , 10%, 15%, 20% from baseline.
- The changes from baseline in body weight, waist circumference, waist to hip ratio (waist/hip circumference), and BMI.
- The percentage change from baseline in body weight (%) after drug withdrawal at the last safe follow-up (W33).
- The changes from baseline in glucose metabolism indicators: HbA1c, FPG, fasting insulin, HOMA-IR and HOMA- $\beta$ .
- The changes from baseline in cardiovascular disease risk factors: blood pressure (systolic and diastolic blood pressure), pulse, TC, LDL-C, HDL-C, and TG.
- The changes from baseline in the impact of weight on quality of life score reported by patients: the total and individual scores of the IWQOL-Lite-CT, the total and individual scores of the physical and psychological parts of SF-36 scoring table.

---

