### 9.2 General statistical consideration

Descriptive statistics such as mean, standard deviation (SD), median, lower quartile (Q1), upper quartile (Q3), minimum and maximum for quantitative variables, and counts and percentages for categorical variables are provided. Critical supporting data are provided in data listings. Unless otherwise stated, all statistical tests (95% CIs) will be two-

sided at a significance level of 0.05, and calculate the corresponding 95% confidence interval (CI). A statistical outlier is defined as a value that is inconsistent with other values and is clinically unreliable. Removal of outliers from analyses requires a thorough justification based on statistical and clinical background. Any outliers are to be reviewed during the blinded EDM (see Section 9.5). All statistical analyses will use SAS 9.4 version or above.

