and the rate of reaching the target and its two-sided 95% CI will be counted in the analysis of the proportion between the two groups. At the same time, the rate difference between the two groups (the investigational drug group and the placebo group) and its two-sided 95% CI will be calculated. The rate of reaching the target and the two-sided 95% CI of the rate difference between the two groups will be calculated by the Clopper-Pearson Exact method.

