### **9.8 Determination of sample size**

Based on the study results of similar drugs and the non-clinical data of GZR18 and the existing clinical human pharmacodynamic data of GZR18, it is estimated that the difference of the percentage of body weight change from baseline at W30 between GZR 18 and placebo group is 11% (GZR18 weight loss of 13%, placebo group weight loss of 2%), the combined standard deviation is 10%, the degree of grasp is 0.8, one-side  $\alpha$  0.025, GZR18 group: placebo group: 4:1, then the calculated sample size is 40 subjects for GZR18 investigational drug and 10 subjects for placebo. Considering the 20% dropout rate, 52 subjects receive GZR18 investigational drug and 13 subjects receive placebo actually. There are five dose groups of GZR18, including the 12 mg/18 mg/24 mg once every two weeks' group and the 24 mg (18 mg) once-weekly group, with 52 subjects in each investigational drug group and 13 subjects in the placebo group; The subjects in the 48 mg once every two weeks' group may not titrate 48 mg due to intolerance to AE, so the number of subjects in the GZR18 group is increased to 78 (65 subjects for the GZR18 investigational drug and 13 people for the placebo group). The total sample size is 338 subjects.

The number of people to be enrolled will be determined based on the assessment of data from nonclinical studies of GZR18 and some data from the clinical trial of GZR18, as well as the number of Phase II clinical trials of similar drugs under development or already marketed, and information considered sufficient by the investigator and sponsor to achieve the trial objectives.

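### The 95% interval for the difference in responder rates is assigned to Clopper-Pearson, a one-sample method that does not define an interval for a difference

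*Protocol*

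**What the plan says.** Section 3.2 lists among the secondary efficacy endpoints the "Proportion of subjects who achieved (yes/no) body weight reduction" of at least 5%, 10%, 15% and 20% from baseline. For these, section 9.4 plans the number and rate of responders with a 95% interval, and adds that "the rate difference between the two groups (the investigational drug group and the placebo group) and its two-sided 95% CI will be calculated". It then fixes the method: "the two-sided 95% CI of the rate difference between the two groups will be calculated by the Clopper-Pearson Exact method". The synopsis (section 1.1, efficacy evaluation) has the same sentence. Section 9.2 sets the general level: tests and intervals are two-sided, at 0.05 and 95%.

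On group sizes, section 9.8 describes the 12, 18 and 24 mg two-weekly groups and the weekly group "with 52 subjects in each investigational drug group and 13 subjects in the placebo group", and gives the 48 mg group 65 and 13. No other method for a difference of proportions appears in the protocol, and there is no rule for combining single-group limits.

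**The concern.** Clopper-Pearson inverts a single binomial test. Its input is one count and one denominator, and its output is an interval for one proportion. A difference of two independent proportions has two counts, two denominators and an unknown nuisance rate, and the method says nothing about how to treat them.

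The sentence therefore cannot be carried out as written. An analyst must either improvise a combination of the two sets of limits or substitute a different, separately named method. This interval is the only between-group analysis that the protocol gives for the responder endpoints. If the method is chosen only once the data are known, the width of the interval, and in sparse cases whether it contains zero, depends on that choice.

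**Working it through.** The protocol states no figure on this point, so there is nothing to reproduce. The check concerns what the method defines and how far the possible substitutes differ.

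**Inputs from the protocol.** 52 drug and 13 placebo subjects per dose group (section 9.8); two-sided 95% (section 9.2). If the placebo subjects of all five dose groups are pooled, 5 × 13 = 65.

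**Inputs assumed.** Responder counts and true responder rates. The protocol gives none.

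**Formulas.**
- Clopper-Pearson for x of n: lower = 0.025 quantile of Beta(x, n − x + 1); upper = 0.975 quantile of Beta(x + 1, n − x). For x = 0 the lower limit is 0 and the upper is 1 − 0.025^(1/n). Only one pair (x, n) enters.
- Subtraction of limits: (L1 − U2, U1 − L2).
- Square-and-add, with d = p1 − p2: lower = d − √[(p1 − L1)² + (U2 − p2)²]; upper = d + √[(U1 − p1)² + (p2 − L2)²].
- Newcombe hybrid-score: the square-and-add formula with Wilson score limits in place of Clopper-Pearson limits.

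**Example A: 15/52 against 0/13 (d = 0.288).** Clopper-Pearson limits are 0.171 to 0.431 for drug and 0 to 0.247 for placebo. Wilson limits are 0.183 to 0.423 and 0 to 0.228.
- Subtraction: 0.171 − 0.247 = −0.08 to 0.43.
- Square-and-add on Clopper-Pearson: 0.288 − √(0.117² + 0.247²) = 0.015, to 0.43.
- Newcombe: 0.288 − √(0.105² + 0.228²) = 0.04, to 0.42.

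**Example B: 42/52 against 3/13 (d = 57.7 points).** Clopper-Pearson gives two separate intervals, 67.5% to 90.4% and 5.0% to 53.8%. For the difference, in percentage points:
- Subtraction: 13.7 to 85.3.
- Square-and-add on Clopper-Pearson: 24.2 to 78.1.
- Newcombe: 27.7 to 74.8.
- Miettinen-Nurminen: 27.9 to 76.3.

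**Coverage and mean width, by exact enumeration of all outcomes, 52 against 13, true rates 60% and 10%.**

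| Interval | Coverage | Mean width |
|---|---|---|
| Subtracted Clopper-Pearson limits | 99.8% | 0.64 |
| Square-and-add on Clopper-Pearson | 97.5% | 0.48 |
| Newcombe | 95.1% | 0.44 |

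Over four assumed pairs of rates (80/20, 60/10, 50/5 and 30/2%), subtraction covers 99.4 to 99.8%, square-and-add about 97 to 98%, and Newcombe 94.7 to 96.1%.

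**Pooled placebo, 52 against 65.** Over the same four pairs, subtraction still covers 99.1 to 99.7%. For 15/52 against 0/65 the Clopper-Pearson upper limit for placebo falls to 1 − 0.025^(1/65) = 0.055 (Wilson 0.056), and the lower limits become:
- Subtraction: 0.171 − 0.055 = 0.12.
- Square-and-add: 0.288 − √(0.117² + 0.055²) = 0.16.
- Newcombe: 0.288 − √(0.105² + 0.056²) = 0.17.

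All three exclude zero.

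**How likely is an empty placebo cell?** Section 9.8 assumes a 2% mean placebo loss and a combined SD of 10%. If losses are taken as normal (an assumption), P(loss ≥ t) = 1 − Φ((t − 2)/10). This gives 21.2% at t = 10, 9.7% at t = 15 and 3.6% at t = 20. The chance of no responder among 13 is (1 − P)^13: about 5%, 27% and 62%.

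**The case against.** Four points can be made for the plan.

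- **It may be a slip of wording.** Taken literally, the sentence also says that the responder rate itself is calculated by Clopper-Pearson, so it may have run two intervals together, with the method meant for the rates only. The SAP, not shown here, could name a two-sample method. This lowers the practical risk. It does not make the text right: the protocol names the interval of the difference, in two places, so a SAP with a valid method would contradict it and one that copied the sentence would inherit the error.
- **Usable intervals can be built from Clopper-Pearson limits.** Square-and-add is a reasonable one, close to Newcombe in the table above. Exact unconditional intervals for a difference also exist. But these are distinct methods, and the protocol names none of them.
- **The comparator may not be 13.** Section 9.4 defines the control mean over the placebo subjects of the first to fifth dose groups, so pooling to 65 is a live reading, although section 9.8 sizes each dose group with its own 13. Under pooling the methods agree on excluding zero in the 15/52 example. Over-coverage by subtraction remains.
- **Little depends on it.** The hypotheses and the one-sided level in section 9.4 concern percentage weight change only, and both improvised intervals err on the wide side, so they do not inflate claims of benefit. This stands.

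**Conclusion.** The method named for the rate-difference interval does not define one. That is a wrong statement in the protocol, not a detail left to the SAP. It should be fixed, but it does not threaten the trial's main conclusion: the effect is confined to the secondary responder endpoints, and the primary ANCOVA, the sample size, the responder-rate point estimates and the single-group intervals are unaffected.

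The size of the effect rests on assumed responder rates and on which placebo group is the comparator. At 52 against 13 and 60% against 10%, mean width runs from 0.44 to 0.64 depending on the construction.

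A reader might infer more than this, in two ways. One is that the text forces subtraction of limits, so that a real difference such as 15/52 against 0/13 would be lost. The protocol never specifies subtraction; square-and-add on the same limits excludes zero there, and a pooled placebo removes the contrast altogether. The other is that placebo will probably have no responders at the higher thresholds, so the choice of method would settle the result. On the protocol's own 2% mean and 10% SD, with normality assumed, an empty cell among 13 is more likely than not only at the 20% threshold.

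**What to change.** In section 9.4 and in the synopsis (section 1.1), split the sentence in two. Keep the Clopper-Pearson interval for each group's responder rate. For the drug-placebo difference, name one two-sample method, for example Miettinen-Nurminen; the Newcombe hybrid-score interval would also serve. State in the same place whether the comparator is the dose group's own 13 placebo subjects or the pooled 65, since the width depends on it. Make the change before unblinding and carry the same wording into the SAP.

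The cost is one sentence in two places. Design, conduct and data collection do not change, and the intervals are standard software options.

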### **Sensitivity analysis**

Sensitivity analysis of main efficacy indicators. The Mixed Model Repeated Measures (MMRM) method will be used to incorporate all time points from baseline to week 30 into the Linear Mixed model (LMM) as a supporting analysis to compare the efficacy differences between the treatment group and the placebo group. Consistent with the primary endpoint analysis method, some specific populations are excluded for comparison of efficacy between groups.

## **9.6 Handling of protocol deviations**

A blinded DEM will be held prior to unblinding of the clinical database and the study after all eCRFs are retrieved and entered and the queries are resolved. The objectives of the blinded DEM are to assess the quality of data from subsequent database locks, identify protocol deviations, identify analysis populations, agree on summary of statistical analysis

stratification levels, and verify the appropriateness of statistical hypothesis for the primary analysis.

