### 6.3.2 Blinding

The frequency and dosage of administration in this study are in an open form. In order to reduce bias, this study adopts a double-blind design (i.e., both the investigator and the subjects are blinded) for the subjects who are given GZR18, or placebo within each group. The investigator and the subjects are always blinded to whether GZR18 or placebo is

administered to the subjects throughout the trial, and the safety of GZR18 and placebo is evaluated in a blinded manner, so as to reduce the subjective bias in the study results.

The color of the solution, the smell, the appearance of the packaging (size and color) of GZR18 and placebo will be identical, so that neither the investigator nor the subject will be able to tell whether the subject is receiving GZR18, or placebo.

Kit numbers will be assigned at Gan & Lee Pharmaceuticals or the Clinical Trial Supply Department of the CRO entrusted by Gan & Lee based on the packaging list generated by the validation procedure. This list will be provided to IVRS/IWRS.

Gan & Lee Pharmaceuticals (or designee) will generate the treatment randomization scheme in a manner that will ensure the study team remains blinded according to current Standard Operating Procedure (SOP). The randomization scheme will be kept in a secure place until the unblinding study is conducted for final statistical analysis.

The sponsor, research centers, and staff of Contract Research Organization (CRO) involved in this study are all blinded to the treatment code with the following exceptions:

- ✓ Sponsor's workforce and its subcontractors directly involved in IMP packaging or IVRS/IWRS management.
- ✓ The Pharmacovigilance (PV) staff will be allowed to have access to the IWRS separately to meet their requirements for reporting SAEs to regulatory authorities.

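### The data evaluation meeting decides outlier removal, and may agree strata and check the primary hypothesis, after all data are in and with dose group open

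*Protocol*

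**What the plan says.** **Timing and remit (Protocol 9.6).** "A blinded DEM will be held prior to unblinding of the clinical database and the study after all eCRFs are retrieved and entered" and queries are resolved. Besides judging data quality and identifying deviations, the meeting is to "identify analysis populations, agree on summary of statistical analysis" stratification levels, and to "verify the appropriateness of statistical hypothesis for the primary analysis".

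**Outliers (9.2).** "A statistical outlier is defined as a value that is inconsistent with other values and is clinically unreliable". No numerical rule is given. Removal needs a full statistical and clinical justification. The review is placed at the same meeting: "Any outliers are to be reviewed during the blinded EDM (see Section 9.5"). Section 9.5 is the PK analysis; the meeting is described in 9.6.

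**What the blind covers (6.3.2).** "The frequency and dosage of administration in this study are in an open form". Within a group, "The investigator and the subjects are always blinded to whether GZR18 or placebo is" given. Allocation is 4:1 in four groups and 5:1 in the 48 mg group (6.3.1). Random numbers carry a dose-group prefix (Table 6-3), and data reaching the sponsor are identified by random number (10.5).

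**What is already fixed.** Section 9.1 defines the FAS as randomised and dosed at least once. Section 9.4 sets the endpoint, one-sided 0.025, five drug means, an ANCOVA with baseline weight and group, and FAS as the basis. It describes the placebo mean as that of the first to fifth dose groups, which reads as pooled placebo.

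**The concern.** A blinded review before unblinding protects the analysis because the people making late judgements cannot tell which way those judgements move the result. Here that protection is partial. Anyone holding a listing by group can see how each dose performed, since about four in five subjects in it are on drug. A listing without a dose column still shows the group through the random-number prefix.

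The remit at that point includes three matters of judgement:

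- which values are outliers and may be removed;
- which stratification levels are agreed, although neither the randomisation nor the primary ANCOVA names a stratum, so this refers to nothing fixed in the protocol;
- whether the primary hypothesis is appropriate, with no rule for what follows if it is judged not to be.

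If such judgements follow the visible group results, the one-sided 0.025 level no longer describes the test against pooled placebo.

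**Working it through.** **1. Group sizes and share on drug (9.8, Table 6-1).** Placebo: 10/(1 − 0.20) = 12.5, rounded up to 13. Drug at 4:1: 4 × 13 = 52. Total: 4 × 65 + 78 = 338, which reproduces the plan. Share on drug: 52/65 = 80.0%; 65/78 = 83.3%.

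**2. What a group listing shows without codes.** Inputs from 9.8: drug −13%, placebo −2%, SD 10. With share p on drug and N subjects:

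- mean = p(−13) + (1 − p)(−2)
- SD = √(100 + p(1 − p) × 11²)
- recovered drug effect = (mean + 2)/p, if placebo loss is taken as 2%

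| Group | Mean | SD | SE of mean | Recovered effect (SE) | \|z\| |
|---|---|---|---|---|---|
| 4:1, N = 65 | −10.8 | 10.93 | 1.36 | −11 (1.69) | 6.5 |
| 48 mg, N = 78 | −11.2 | 10.81 | 1.22 | −11 (1.47) | 7.5 |

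A difference between two 4:1 groups appears at 80% of its true size. The protocol gives no dose difference, so a range has to be assumed. With 52 evaluable per group (65 less 20% dropout), the SE of the difference is 10.93 × √(2/52) = 2.14. The chance that the visible means are in the right order is Φ(0.8 × difference/2.14):

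| True dose difference (points) | 1 | 2 | 3 | 5 |
|---|---|---|---|---|
| Correct order | 65% | 77% | 87% | 97% |

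**3. What judgement-based removal could do to the error rate.** Simulation with no drug effect, SD 10, and one open group of 52 drug and 13 placebo. The k least favourable values are dropped without knowing the codes. The two-sample t-test is one-sided at 0.025. Pooled placebo adds the 52 placebo subjects of the other four groups.

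| Values dropped | 0 | 1 | 2 | 3 | 5 |
|---|---|---|---|---|---|
| Against own-group placebo | 0.025 | 0.024 | 0.021 | 0.023 | 0.022 |
| Against pooled placebo | 0.026 | 0.037 | 0.052 | 0.061 | 0.105 |

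These are 20,000 runs per cell. A repeat with 100,000 runs gave 0.050, 0.065 and 0.104 against pooled placebo for 2, 3 and 5 values, and 0.023 in all three cases against own-group placebo. Pooling is what creates the inflation: trimming an open group shifts its drug mean, while four fifths of the pooled comparator (52 of 65) lies outside that group and is untouched. Own-group placebo is trimmed by the same blind rule, so the test keeps its level.

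**The case against.** The case against is substantial, and much of it stands.

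- **Verifying is not setting.** Section 9.6 lets the meeting verify the hypothesis, not choose it. Sections 9.1 and 9.4 already fix the main elements, so identifying populations can be read as applying those definitions. A reader might infer that the meeting could settle the primary hypothesis or decide which dose groups are tested. The text does not say so, and 9.4 names all five.
- **Strata may concern layout only.** The phrase can be read as the layout of summary tables, since the primary model has no stratum. If so, deleting it costs nothing.
- **Sensitivity exclusions.** Section 9.4 says that "some specific populations are excluded for comparison of efficacy between groups", but as a sensitivity analysis, and it does not assign the choice to this meeting. Naming those populations can be left to the SAP.
- **Safeguards on outliers.** Section 9.2 requires a value to be both inconsistent and clinically unreliable, with a justification. Dropping the worst values of one group because they are the worst would breach this. The simulation shows how far the result could move, not what would happen.
- **No listing is specified.** Section 9.6 does not say that W30 weight is shown by dose group. Equally, it does not prevent it.
- **The treatment code stays blinded.** Drug versus placebo within a group is masked, including for sponsor and CRO staff apart from the exceptions listed in 6.3.2.

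What remains is that judgement on outliers, and any change made under the hypothesis or strata items, is placed after the data are complete with dose group open. Silence in the SAP is not the issue: the protocol itself gives these items to this meeting.

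**Conclusion.** The point holds in a limited form. The blind at this meeting is weaker than its name suggests, and the exposed decisions are mainly outlier removal, plus anything changed under the strata and hypothesis items. For a test against pooled placebo, dropping 2 to 5 unfavourable values in one open group would move the one-sided error from 0.025 to about 0.05 to 0.11. Against the group's own placebo it stays at about 0.02 to 0.025. This rests on reading 9.4 as pooled placebo, on no drug effect, and on removal directed at one group's least favourable values.

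Two stronger readings should not be drawn.

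- Testing only the best-looking open group against pooled placebo gives 8.6% under no effect. That does not measure the meeting's influence. No section allows such a selection, and the five planned comparisons at unadjusted 0.025 already give about 9.4% for at least one false positive with no one looking at the data. That is a separate multiplicity question.
- A 98% chance of seeing two doses in the right order can be calculated, but only by assuming a 5-point dose difference and all 65 subjects evaluable. The protocol gives no such difference.

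Nor is a blinded data review before unblinding a fault in itself. The weakness is this remit combined with an open dose group.

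**What to change.** **Section 9.6.** Delete the last two objectives, the agreement on stratification levels and the check of the primary hypothesis. Limit the meeting to classifying deviations and applying the set definitions in 9.1. Use listings without dose group and without W30 weight, and recode the random number, because its prefix gives the group away. A yes/no flag for an available W30 weight is enough for the per-protocol definition.

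**Section 9.2.** Keep all values in the primary FAS analysis unless source documents show a recording error. Present results without outliers only as a sensitivity analysis. Correct the cross-reference from 9.5 to 9.6.

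**Cost.** A wording amendment made before the meeting and one stripped listing. The sponsor gives up some freedom to adapt the analysis late.
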